### Service use

The Cost of Illness Inventory (COII) captures costs related to education, childcare, relocation, healthcare contacts (outpatient, inpatient, medical emergencies, investigations and medication), religious retreats and rituals, specialist equipment, workshops and training, special diet, support and care, certification, occupational adjustments and government rebates/schemes [23].

### COVID-19 Impact Questionnaire

The COVID-19 Impact Questionnaire was added after the COVID-19 pandemic to understand the impact of the pandemic and associated lockdowns on the families.

The adverse event form covers reporting of adverse events where there is any safety concern for participants as well as anything relevant to the continuation of the study or where the principal investigators (PIs) feel that the data monitoring and ethics committee (DMEC) should be informed.

### Changes to evaluation procedures due to COVID-19 pandemic

In response to the major disruption throughout India and especially in NCT of Delhi in access to communities and households caused by the COVID-19 pandemic, we implemented changes to research procedures. The intense advocacy for social distancing, perceived health risks and widespread stigma made in-person contacts with trial participants infeasible in the study area. Considering these evolving situations changes in the trial’s assessment procedures were proposed in August 2020 to enable continuation of participant recruitment and assessments.

#### Hybrid evaluation schedule

Majority assessments that were earlier administered in person were planned to be conducted via telephonic interviews. Audio records of informed consent were taken. Detailed procedures were developed for secure storage and sharing of consent information. There were no changes in outcome measures of the trial; however, for ascertaining eligibility in terms of age equivalence, the motor skill domain of Vineland 3 was used as a replacement for Mullen Scales of Early Learning. The RAFIN was dropped given its relative difficulty with administration over phone. A COVID-19 Impact Questionnaire was added to understand the impact of the pandemic and associated lockdowns on the trial families. All assessments were planned over five contacts—four telephonic and one in-person (preferably in the office, if not, then at participant’s home).

Adequate precautions including routine sanitisation of assessment rooms and kits before and after assessments, providing sanitised office transportation to participants, regular temperature checks of all team members and visiting families, supporting COVID-19 tests and vaccination of team members and use of transparent masks during in-person assessments were taken to minimise exposure to COVID-19 for both participants and assessors.

Adapting the evaluation plan allowed trial assessments to continue in a situation where home visits in the community were not possible. Telephonically contacting families reduced the chances of exposure to COVID-19. However, in situations where telephonic interviews were not possible and there was mutual agreement to undertake home visits, assessors visited participants in communities. This has particularly been possible in the second quarter of 2022 which has seen reduction in COVID cases in the NCT of Delhi. Furthermore, continuing evaluations also ensures maintenance of competency of the trained assessors.

#### Adapting assessment timepoints

As per original trial protocol, endline assessments were to be conducted between 9 and 12 months from randomisation. However, due to COVID-19-related lockdowns and restrictions, for a subset of participants who were affected by trial pause, an additional 4 months will be added to this assessment window. Thus, for such participants, the endline assessments will be conducted between 13 and 16 months from randomisation.

For participants whose assessments will not be completed in the given time, an additional month was given; failing which, all such participants were classified as endline missed. These participants were then approached for follow-up assessments.

Follow-up assessments for the trial families were scheduled at 15 months from randomisation. However, similar to the impact of a trial pause on the endline, for a subset of participants, an additional 4 months will be added which shifted the follow-up start point from 15 to 19 months. Additionally, a minimum gap of 3 months will be ensured between the completion of end line assessments and start of follow-up assessments.

#### Trial update as on March 2023

The COMPASS trial completed randomisation of 261 participants on 16 December 2022. As of 31 March 2023, 157 (60%) endpoint assessments were completed and 30 participants (11.5%) were lost to follow-up. Also, 86 (33%) follow-up assessments (15 months post randomisation) were completed by the end of March 2023.

Adaptation to the assessment processes were made during the COVID-19 pandemic-related restrictions (these are detailed the above section). It has taken relatively more time to complete the telephonic assessments compared to in-person contacts. Telephonic assessments take between 4 and 6 contacts with each participating family; every contact takes around 60 min and an additional in-person contact for BOSCC, DCMA and START administration. In-person assessments are completed in 3 contacts, each ranging from 60 to 90 min. In both cases, the number of contacts and the time duration can vary depending on the family’s need and availability. However, it is also important to note that the method of administration of the primary trial outcome, i.e. the BOSCC has remained same throughout the trial (Table 1).

**Table 1 Tab1:**
[figure not shown]
Schedule of assessments (revised to reflect pandemic-related adjustments)

^*^Specific changes made due to COVID-19 related restrictions

## Participant timeline {13}

[figure not shown]

### Sample size {14}

The trial is powered based on data from the PACT, PASS and PASS + trials, along with conservative assumptions on context and implementation. The UK PACT showed an endpoint ES of 0.64 on autism symptoms and 0.55 over 6 years. The PASS trial did not measure autism symptom outcomes, but its effect on the intermediate dyadic interaction outcomes that mediated autism symptom change was equivalent to the PACT study. Given the possible challenges of implementation at scale in India using existing health system workers and health system-like workers, in COMPASS, we hypothesise a conservative target effect size of 0.45 for BOSCC symptoms (representing a clinically relevant 5-point change) [16]. We further assume a conservative intra-cluster correlation of 0.02 to account for variation in therapist quality and clustering amongst the 20 intervention therapists, each seeing on average 8 participants (TAU participants treated as clusters of size 1 with ICC 0) [24]. Given these assumptions, 96 successfully followed up in each group would give 90% power to detect an effect size of 0.45SD and 85% power for effect size of 0.37 SD (two-tailed significance level 0.05 and *t*-test assumed, using Stata ‘clsampsi’). Our pilot studies showed attrition rates leading to endpoint missingness of 3/65 (4.6%) in a semi-urban setting (PASS) and 6/40 (15%) in a rural setting (PASS +). We have modelled a conservative 20% attrition in this study in a large city, giving a recruitment target of 240 patients, making this trial larger than any yet published in the autism psychosocial intervention literature. Mediation effects were shown in the UK PACT trial with a comparatively smaller *n* = 152.

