**Methods:**

The Communication-centred Parent-mediated treatment for Autism Spectrum Disorder in South Asia (COMPASS) trial is now a scale-up two-centre, two-arm single (rater) blinded random allocation parallel group study of the PASS Plus intervention in addition to treatment as usual (TAU) compared to TAU alone, plus health economic evaluation embedded in the India health system. Two hundred forty children (approximately 120 intervention/120 TAU) with ASD aged 2–9 years will be recruited from two tertiary care government hospitals in New Delhi, India. Accredited Social Health Activists will be one of the intervention delivery agents. Families will undertake up to 12 communication sessions over 8 months and will be offered the Plus modules which address coexisting problems. The trial’s primary endpoint is at 9 months from randomisation, with follow-up at 15 months. The primary outcome is autism symptom severity; secondary outcomes include parent–child communication, child adaptation, quality of life and parental wellbeing. Primary analysis will follow intention-to-treat principles using linear mixed model regressions with group allocation and repeated measures as random effects. The cost-effectiveness analysis will use a societal perspective over the 15-month period of intervention and follow-up.

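### The clustering inputs to the sample size do not agree: 20 therapists averaging 8 children each is 160, but the intervention arm is about 120 recruited and 96 analysed

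*Protocol article*

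**What the plan says.** The section Sample size {14} of the protocol article sets the clustering allowance. "We further assume a conservative intra-cluster correlation of 0.02", it says, to cover variation in therapist quality and "clustering amongst the 20 intervention therapists, each seeing on average 8 participants". The control arm carries no clustering: "TAU participants treated as clusters of size 1 with ICC 0".

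The arm sizes are given in two places that agree with each other. The sample-size section states that "96 successfully followed up in each group would give 90% power to detect an effect size of 0.45SD", adds "85% power for effect size of 0.37 SD", and uses a "two-tailed significance level 0.05" and a t-test. It allows for 20% attrition and reaches a target of 240. The abstract (Methods) has "Two hundred forty children (approximately 120 intervention/120 TAU". The trial update of March 2023 reports that 261 children were randomised.

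**The concern.** A caseload that applies to the intervention arm alone, multiplied by the number of therapists, should return the size of that arm. Here it returns 160, which is 40 more than the roughly 120 to be allocated and 64 more than the 96 to be analysed. Attrition cannot bridge the gap, because the 20% loss already accounts for the step from 120 to 96.

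Caseload and ICC together set the design effect, so one input to the stated power is wrong as written. Anyone reproducing the calculation has to decide which of therapist number and caseload to believe. If the power figures in that section are corrected while this sentence stays, the corrected figures will still rest on inputs that do not describe one trial.

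**Working it through.** **Inputs, all from the protocol article.** Therapists k = 20, mean caseload m = 8, ICC = 0.02 in the intervention arm and 0 in the control arm, 96 analysed per arm, effect sizes 0.45 and 0.37 SD, two-sided 5% level, t-test, 20% attrition (Sample size {14}). About 120 allocated per arm (abstract). 261 randomised (trial update).

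**Step 1: the recruitment target reproduces.** 96 / 0.8 = 120 per arm, and 2 × 120 = 240. Arm size is consistent within the section and with the abstract.

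**Step 2: the therapist figures do not fit that arm.**
- As stated: 20 × 8 = 160. 160 − 120 = 40 and 160 − 96 = 64.
- Keeping 20 therapists: 120 / 20 = 6 recruited, 96 / 20 = 4.8 analysed.
- Keeping a caseload of 8: 120 / 8 = 15 therapists, 96 / 8 = 12 at analysis.
- With the 261 randomised, assuming a near-equal split: 261 / 2 = 130.5, and 130.5 / 20 ≈ 6.5. This is still below 8.

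**Step 3: design effect in the intervention arm,** DE = 1 + (m − 1) × ICC.
- m = 8: 1 + 7 × 0.02 = 1.14
- m = 6: 1 + 5 × 0.02 = 1.10
- m = 4.8: 1 + 3.8 × 0.02 = 1.076

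**Step 4: power with 96 per arm.** In SD units, SE = √(DE/96 + 1/96). The noncentrality is the effect size divided by SE, with a noncentral t on 96 + 96 − 2 = 190 degrees of freedom.

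| Caseload | DE | SE | 0.45 / SE | Power at 0.45 SD |
|---|---|---|---|---|
| 8 (as stated) | 1.14 | 0.1493 | 3.014 | 85.1% |
| 6 | 1.10 | 0.1479 | 3.043 | 85.7% |
| 4.8 | 1.076 | 0.1471 | 3.060 | 86.1% |
| no clustering | 1.00 | 0.1443 | 3.118 | 87.3% |

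Correcting the caseload moves power up by 85.7 − 85.1 = 0.6 points (m = 6) or 86.1 − 85.1 = 1.0 point (m = 4.8).

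**Step 5: comparison with the plan's power.** The stated 90% at 0.45 SD does not reproduce from the stated inputs, and removing clustering altogether leaves it at 87.3%. At 0.37 SD the same method gives about 69% (m = 8) to 71% (m = 4.8), and 72.3% with no clustering, against the stated 85%. The gap between the stated and the reproduced power therefore does not come from the caseload.

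**The case against.** The strongest reply is that the slip does no harm. A caseload of 8 is larger than the arm can support, so it inflates the design effect and understates power by about a point at most. The calculation errs on the cautious side. This stands, and it limits the weight of the point. The document does not, however, present 8 as a deliberate upper bound. It calls the ICC, the target effect and the attrition conservative, but gives the caseload as an average.

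A second reply is that children might see more than one therapist, since the cost-effectiveness section anticipates attrition of front-line workers. The document does not say that each child has a single therapist, so the figures are better called mutually inconsistent than impossible. Equally, nothing in it says that caseloads were counted with overlap. The practice families mentioned under the pandemic modifications are placed outside the trial, so they do not explain the figure either.

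A reader might go further and infer that the arm size is ambiguous, or that an arm of 160 was entered and produced the 90%. The text does not support this. It gives "96 successfully followed up in each group", and that figure leads exactly to 120 per arm and 240 in total. Larger consequences can be produced only with an ICC well above 0.02 or with an enlarged intervention arm, and the plan proposes neither.

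**Conclusion.** The inconsistency is real. With one therapist per child, 20 therapists, a mean of 8 children each and an intervention arm of 120 (96 analysed) cannot all be true, and no other text reconciles them. Its size is small and in the safe direction: a design effect of 1.14 as stated against 1.10 or 1.076, and power at 0.45 SD of 85.1% against 85.7% or 86.1%.

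These figures assume the stated ICC of 0.02, equal caseloads, 96 analysed per arm and the unadjusted t-test that the section names. The sentence needs correcting because it is a stated input to the sample size. It does not weaken the trial's design, and it is not the cause of the overstated 90%. Since that figure is not supported by the inputs on either caseload, the two should be put right together.

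**What to change.** Correct either the therapist number or the mean caseload in Sample size {14} so that their product matches the intervention arm. That means 20 therapists with a mean of 6 recruited (4.8 analysed), or a caseload of 8 with 15 therapists (12 at analysis). Alternatively, report the actual number of counsellors and their mean caseload for the 261 randomised. Then re-run the calculation with 96 per arm and restate the design effect and the power that result, which is about 85–86% at 0.45 SD in place of 90%. The power at 0.37 SD should be restated from the same run.

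The cost is one corrected sentence and one re-run. Recruitment, which is already complete, is unaffected.

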### Extension to co-occurring conditions

Subsequently, the team in India developed and piloted an enhancement of PASS which included a clinical decision algorithm containing strategies to address common co-occurring conditions in autistic children. These included sensory-seeking and disruptive behaviours (identified in the PASS trial as potential barriers to implementation and acceptability in low-resource settings), creating a comprehensive intervention for children with ASD in the 2–9-year age group (PASS Plus; PASS +). The pilot RCT of PASS + (The PASS + study; 2014–2016; Grand Challenges Canada) [10] demonstrated feasibility by meeting its recruitment target of 40 children in a rural setting; the intervention was delivered successfully with fidelity to 19 families randomised to intervention. Eighty-nine percent of intervention families partially or entirely completed the 12-session intervention. Intention-to-treat analysis showed a reduction in mean scores of autism symptom severity, though the confidence interval contained zero (adjusted mean difference [AMD] 2.42; 95% CI − 7.75, 2.92; ES 0.22); large treatment effects on proximal outcomes of proportion of parent synchronous responses (AMD 0.35; 95% CI 0.18, 0.52; effect size ES 3.97) and proportion of child communication initiations with parent (AMD 0.17; 95% CI 0.03, 0.32; ES 1.02). Confidence intervals for effects on mutual shared attention (AMD 0.10; 95% CI − 0.07, 0.27; ES 0.5) and co-morbid symptoms (AMD − 9.0; 95% CI − 24.26, 6.26; ES 0.32) contained zero.

Both these projects have enabled the India team to capacity build in training and supervision of non-specialist health workers. Evaluation methods have also been adapted and tested in both of these pilot studies, including the Brief Observation of Social Communication Change (BOSCC), the primary outcome measure to be used in COMPASS. The project team in India will preserve competence in delivery, analysis and dissemination seamlessly into COMPASS, minimising the risk of loss of capacity.

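### The stated power (90% at 0.45 SD, 85% at 0.37 SD) does not follow from the stated inputs, which give about 85% and 69%; the two figures also contradict each other

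*Protocol article*

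**What the plan says.** The Sample size section sets a target difference of 0.45 SD on the BOSCC and assumes "96 successfully followed up in each group". It applies an intra-cluster correlation of 0.02 to the intervention arm, with "20 intervention therapists, each seeing on average 8 participants". TAU children count as clusters of one with no correlation. The test is a t-test at a "two-tailed significance level 0.05", computed with a Stata routine for clustered samples. The section concludes that this sample "would give 90% power to detect an effect size of 0.45SD and 85% power for effect size of 0.37 SD". Allowing for 20% attrition, it arrives at 240 children, which the abstract divides into roughly 120 per arm.

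Two other places bear on the point. Statistical methods for primary and secondary outcomes specifies a mixed model with the baseline outcome, centre and age group as covariates. The March 2023 trial update reports that 261 children were randomised.

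**The concern.** Every input needed to reproduce the power is given, so the claim can be checked directly. Two features look wrong before any detailed calculation. First, reducing the effect from 0.45 to 0.37 SD, by nearly a fifth, is said to cost only 5 points of power, which is too little near 90%. Second, 20 therapists with 8 children each makes 160 children, more than the intervention arm contains.

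At stake is how readers judge the trial's planned sensitivity. The Discussion describes the evaluation as well powered, and the results paper is likely to repeat the sample-size statement. A reader of a null result would take from it that the planned design had only a 15% chance of missing 0.37 SD. The stated assumptions do not give that assurance.

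**Working it through.** **Inputs, all from Sample size:** n = 96 per group; two-sided alpha 0.05; t-test; intra-cluster correlation 0.02 in the intervention arm and 0 in TAU; m = 8 children per therapist; effects of 0.45 and 0.37 in SD units.

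**Step 1. Attrition.** (96 + 96) / 0.8 = 240. The stated recruitment target is reproduced.

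**Step 2. Standard error under the stated inputs.**
- Design effect, intervention arm: 1 + (8 − 1) × 0.02 = 1.14. For TAU it is 1.
- SE = √(1.14/96 + 1/96) = √(2.14/96) = 0.1493 SD.

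**Step 3. Power (noncentral t, 190 degrees of freedom).**
- 0.45 SD: 0.45 / 0.1493 = 3.01, power 85.1% (stated 90%).
- 0.37 SD: 0.37 / 0.1493 = 2.48, power 69.3% (stated 85%).
- The normal approximation gives 85.4% and 69.8%.
- Effect detectable with 90% power: 0.486 SD, about 0.49.

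**Step 4. Can another reading reproduce the stated pair?**

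| Reading | 0.45 SD | 0.37 SD |
|---|---|---|
| As stated (m = 8) | 85.1% | 69.3% |
| m = 6 (120/20) | 85.7% | 70.2% |
| m = 4.8 (96/20) | 86.1% | 70.7% |
| No clustering | 87.3% | 72.3% |
| One-sided 0.05, m = 8 | 91.3% | 79.5% |
| 120 per group, no attrition | 91.9% | 78.8% |
| 160 intervention v 96 TAU | 92.3% | 79.5% |
| 160 v 160 | 97.3% | 89.1% |
| **Stated** | **90%** | **85%** |

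None gives both figures. The no-clustering row is the most favourable that a two-sided t-test with 96 per group allows.

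**Step 5. Internal consistency.** In one design the SE is the same for both effects, so the ratio of effect to SE scales with the effect (normal approximation).
- 90% at 0.45 SD needs a ratio of 1.960 + 1.282 = 3.242. At 0.37 SD the ratio is 3.242 × 0.37/0.45 = 2.665, and 2.665 − 1.960 = 0.705, which is 76% power.
- 85% at 0.37 SD needs 1.960 + 1.036 = 2.996. At 0.45 SD the ratio is 2.996 × 0.45/0.37 = 3.644, and 3.644 − 1.960 = 1.684, which is 95% power.

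This does not depend on the correlation within therapists, the outcome SD or the covariates.

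**Step 6. Baseline adjustment.** The article gives no baseline-endpoint correlation r, so these values are assumptions. Multiplying the variance by 1 − r², with 96 per group and m = 8:
- r = 0.4: 90.5% and 76.7%.
- r = 0.5: 93.4% and 81.2%.
- r = 0.6: 96.3% and 86.9%.

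Reaching 90% at 0.45 SD needs r of about 0.38; reaching 85% at 0.37 SD needs about 0.57. No single r yields the stated pair.

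**Step 7. The 261 randomised.** At the planned 20% attrition, which is an assumption here, 261 × 0.8 / 2 = 104.4 per group. The same t-test (m = 8) then gives about 88% and 73%.

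**The case against.** The strongest reply is that the planning t-test is not the trial's analysis. The primary model adjusts for baseline BOSCC, and at r of about 0.6 both stated powers would be met or exceeded. This stands as a limit on what can be concluded. A reader might infer that the trial's actual type II error is 15% at 0.45 SD and 31% at 0.37 SD. The documents do not support that, because those figures belong to the unadjusted t-test. The reply does not rescue the statement itself, which attributes its figures to a t-test, names no correlation and would need two different ones.

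A second reply is that little turns on the error. Recruitment is complete, more children were randomised than planned, 0.45 SD is the target and 0.37 SD only an illustration, and results will be reported with confidence intervals. This stands as to consequence: no analysis or decision rule changes.

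Third, the caseload mismatch is immaterial. That is right for power. Replacing 8 with 6 or 4.8 raises it by at most 1.4 points, so the larger caseload errs on the cautious side.

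A reader might also set the "conservative target effect size of 0.45 for BOSCC symptoms" against the PASS+ pilot's 0.22 and conclude that the target is contradicted. It is not. That pilot had 40 children, its interval (−7.75 to 2.92) includes a 5-point benefit, and the article reports it openly. The target is set below the UK trial's 0.64 and 0.55 and tied to a 5-point change regarded as clinically relevant.

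**Conclusion.** The power statement is wrong as written. Under the section's own assumptions, power is about 85% rather than 90% at 0.45 SD, and about 69% rather than 85% at 0.37 SD. The first gap is moderate. The second is too large for rounding, clustering or choice of approximation to explain. Whatever the assumptions, at least one of the two figures must be false.

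The 85% and 69% rest on the stated inputs and an unadjusted t-test; they do not measure the power of the planned mixed model. The article does not show how the error arose. Since 85% is what the stated design gives at 0.45 SD, a mixed-up figure is possible but cannot be confirmed. The product of 160 children is a separate slip with negligible effect on power, and the text does not show whether the number of therapists or the caseload is at fault.

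**What to change.** Re-run the calculation, report its inputs, and restate the result along these lines: with 96 followed up per group, an unadjusted two-sided t-test has about 85% power for 0.45 SD and about 69% for 0.37 SD, and reaches 90% at about 0.49 SD. Remove the claim of 85% power at 0.37 SD.

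If baseline adjustment is to be credited, state the assumed correlation and its source, and give both powers under that one value (for example about 90% and 77% at r = 0.4, or 96% and 87% at r = 0.6).

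Reconcile the number of therapists and the caseload with the roughly 120 children in the intervention arm. If power is quoted for the 261 randomised, label it as depending on assumed attrition (about 88% and 73% at the planned 20%, t-test).

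The cost is a reworded paragraph here and in any later paper that quotes it, with a less favourable stated power. Recruitment, conduct and analysis are unaffected.
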